## Abstract

**Background:**

Children with neurological impairment may have dysphagia and/or gastro-esophageal reflux disease (GERD), which predispose to complications affecting the airways, increasing risk for aspiration-induced acute and chronic lung disease, or secondarily malnutrition, further neurodevelopmental disturbances, stressful interactions with their caregivers and chronic pain. Only multidisciplinary clinical feeding evaluation and empirical trials are applied to provide support to the management of feeding difficulties related to dysphagia or GERD, but no standardized feeding or behavioral measure exists at any age to assess aspiration risk and support the indication to perform a videofluoroscopic swallowing study (VFSS) or a fibre-optic endoscopic examination of swallowing (FEES), in particular in newborns and infants with neurological impairments. Lung ultrasound (LUS) has been proposed as a non-invasive, radiation-free tool for the diagnosis of pulmonary conditions in infants, with high sensitivity and specificity.

**Methods:**

A RCT will be conducted in infants aged between 0 and 6 years having, or being at risk for, cerebral palsy, or other neurodevelopmental disease that determines abnormal muscular tone or motor developmental delay assessed by a quantitative scale for infants or if there is the suspicion of GERD or dysphagia based on clinical symptoms. Infants will be allocated in one of 2 groups: 1) LUS-monitored management (LUS-m); 2) Standard care management (SC-m) and after baseline assessment (T0), both groups will undergo an experimental 6-months follow-up. In the first 3 months, infants will be evaluated a minimum of 1 time per month, in-hospital, for a total of 3 LUS-monitored meal evaluations. Primary and secondary endpoint measures will be collected at 3 and 6 months.

**Discussion:**

This paper describes the study protocol consisting of a RCT with two main objectives: (1) to evaluate the benefits of the use of LUS for monitoring silent and apparent aspiration in the management of dysphagia and its impact on pulmonary illness and growth and (2) to investigate the impact of the LUS management on blood sample and bone metabolism, pain and interaction with caregivers.

**Trial registration:**

Trial registration date 02/05/2020; ClinicalTrials.gov Identifier: NCT04253951.

## Background

Children with neurological impairment commonly experience abnormal ingestion functions (WHO, http://apps.who.int/classifications/icfbrowser/), including impairment in oral-motor function, rumination, abnormal swallowing, regurgitation and vomiting, defined as dysphagia and/or gastro-esophageal reflux disease (GERD), delayed gastric emptying and constipation [1, 2]. The number of these children is estimated not to decline in the next years, and their life expectancy to increase [3]. The neurological impairment may arise from a variety of disorders, including cerebral palsy or rare paediatric diseases such as genetic, metabolic, muscular and movement disorders. Primary or secondary muscle tone abnormalities in these disorders contribute to dysphagia and/or GERD, which predispose to complications affecting the airways, increasing risk for insidious development of aspiration-induced acute and chronic lung disease, or secondary malnutrition, further neurodevelopmental disturbances, and stressful interactions with their caregivers [4–6]. Moreover, infants with GERD likely experience chronic pain: inability to settle, grimacing, tense body, hypo- or hyper-reactions to acute pain, and deregulated sleep are possible indicators, even if no current definitions exist that are wholly applicable to infancy [7].

In such patients, a failure to thrive is the sum of nutritional and non-nutritional factors (mainly frequent respiratory infections and chronic pain, as well as use of antiepileptic medication). Malnutrition per se is due to feeding difficulties (with consequent insufficient dietary intake or excessive nutrient losses) and altered energy metabolism, and is associated to micronutrients deficiencies and osteopenia [8]. In the last couple of decades, the nutritional needs of children with neurological impairment have become a major matter of interest so that, in 2017, the European Society of Gastroenterology, Hepatology, and Nutrition (ESPGHAN) published a consensus statement (ESPGHAN guidelines) on the diagnosis and management of gastrointestinal and nutritional complications in children with neurological disability [9]. Both diagnosis of GERD and accurate monitoring of growth and nutritional status are among the “top ten-tips” in managing nutritional issues and gastrointestinal function in neurologically impaired children [10].

Oral fluid, food or refluxed gastric contents can be aspirated into the lungs, apparently, by choking or coughing, or silently. In order to directly or indirectly diagnose aspiration in dysphagia and GERD, video-fluoroscopic swallowing study (VFSS) and fiber-optic endoscopic examination of swallowing (FEES) are options, however they focus on a single study, thus clinical diagnosis is seldom made despite a normal result and, due to radiation exposure, invasiveness and costs, they are poorly reproducible in the same patient [11–13]. Furthermore, rheological and material property parameters among the barium-impregnated liquids and the thickened and unthicken infant formula are different, thus biasing the interpretation of the radiological results and consequent clinical recommendations [13, 14]. Finally, only clinical feeding evaluation and empirical trials are applied to provide support to the management of feeding difficulties related to dysphagia or GERD, and no standardized feeding or behavioral measure exists at any age to assess aspiration risk and support the indication to perform VFSS or FEES.

The picture is further complicated at young ages, as recently the concept of ‘early diagnosis’ has emerged for cerebral palsy and a variety of neurological disorders [15]. Indeed, most studies focusing on dysphagia and GERD in neurologically impaired children refer to ages older than 1 year. In the few studies investigating dysphagia in infants younger than 1 year by using VFSS, aspiration was present in 50% of infants with suspected dysphagia and up to 90% of them had silent aspiration [16]. This indicates that many infants who are not clinically suspected of having dysphagia or GERD may have silent aspiration, therefore a monitoring would be recommended in infants with higher aspiration risk, starting early from the first days of life. This would lead to earlier diagnosis, clinical management ad tailored habilitation and nutritional strategies to improve outcome and limit short-term and long-term complications [17].

Lung ultrasound (LUS) has been proposed and gained consensus as a non-invasive, radiation-free tool for the diagnosis of acute and chronic pulmonary conditions in both infants and adults, with high sensitivity and specificity in several conditions [18–22] LUS is an easy technique that may be performed during routine physical examination, with a point-of-care approach. Previous studies demonstrated that LUS is able to detect small lung consolidations with very high accuracy [22], and can be effectively used to follow-up the dynamic changes of these lesions. LUS is a patient-friendly tool, especially in young children, who are particularly susceptible to radiation exposure, which can impact later in their life with an increase risk of cancer [23].

The trial is conceived as a double-blinded randomized parallel-designed controlled trial (Consort checklist, [24]), comparing LUS-monitored management and standard care.

We hypothesize infants receiving LUS-monitored management having lower rate of pulmonary illness and better growth curves, and also reduce the need for invasive diagnostic (VFSS/FEES) over time. We also hypothesize infants receiving LUS-monitored management will have better biochemical and bone metabolism results, lower pain indices and less stressful interaction with caregivers.

## Methods

The presented protocol consists of a RCT, which compares LUS-monitored management of dysphagia-related aspiration versus standard care management in infants with neurological impairment. Study timeline is scheduled in Fig. 1.

**Fig. 1 Fig1:**
[figure not shown]
Schedule of study enrolment, interventions, and assessments

The main aim of the presented trial is to explore the effectiveness of the use of LUS for monitoring pulmonary abnormalities related to aspiration during feeding in neurologically impaired infants, by comparing integrated LUS-monitored management of dysphagia to standard care in terms of medical/neurological/behavioral status, chronic pain/discomfort and stress for caregivers.

Specific hypotheses to be tested are:Infants receiving LUS-monitored management will have lower rate of pulmonary illness and better growth curves, corresponding to less after-meal LUS abnormalities over time, compared to infants receiving standard care. They will also reduce the need for invasive diagnostic (VFSS/FEES) over time.Infants receiving LUS-monitored management will have better results at blood sample and bone metabolism, lower pain indices and less stressful interaction with caregivers.

We also hypothesized that diagnostic benefits of LUS-monitored management will contribute to better neurological outcome.

Further aims also include the comparison between LUS and VFSS/FEES in the detection of feeding-related silent or apparent aspiration and to estimate aspiration entity by cut-off values for the diagnosis of clinically significant silent or overt aspiration, responsiveness of LUS monitoring to medical, postural or food consistencies adaptation, and their relationship with standardized clinical feeding evaluation and medical/behavioral/neurological measures. Moreover, we will explore the impact of brain abnormalities detected by brain MRI on LUS findings severity.

We will finally establish risk categories for unsafe swallowing disorders and potential clinical recommendations for early management.

### Participants

A minimum sample size of 126 subjects was determined (63 each group). Newborn and infants will be recruited by the child neurologist and the speech and language pathologist (SLP) from the Infant Neurology Section of academic hospital IRCCS Stella Maris Foundation in Pisa, Italy.

Subjects will be included in the study if: i) they have, or they are at risk for, cerebral palsy [15] or have abnormal muscular tone at any age between 0–6 years of life due disorders other than cerebral palsy; or ii) motor developmental delay assessed by a quantitative scale for infants and young children development (< 5 sd according to age); or iii) in absence of the previous clinical indices, if there is the suspicion of GERD or dysphagia based on clinical symptoms; iv) a brain MRI acquisition done before or programmed prior the end of the study period as part of their diagnostic procedure. Subjects will be excluded in presence of primary chronic lung diseases.

### Procedure

The medical staff of the recruiting center will refer eligible infants to researchers. Researchers will provide parents/guardians detailed information about the study procedures and seek informed consent. Assessments and procedures included in the study will be provided at IRCCS Stella Maris Foundation and Azienda Ospedaliero-Universitaria Pisana (AOUP), Pisa.

Also, the portable LUS machines that is used will allow the opportunity for home LUS evaluation to improve compliance of the patients to the experimental follow-up period.

Key inclusion and exclusion criteria	Ages eligible for study: 0–6 years Sexes eligible for study: both Accepts healthy volunteers: no
	Inclusion criteria: infant and children < 6 years; with, or at risk for, cerebral palsy or abnormal muscular tone due disorders other than cerebral palsy; suspicion of GERD or dysphagia based on clinical symptoms
	Exclusion criteria: primary chronic lung diseases
Study type	Interventional
	Allocation: randomized intervention model. Double blind (caregiver, outcomes assessor)
	Primary purpose: early diagnosis
Date of first enrolment	April 2021
Target sample size	150
Recruitment status	Recruiting

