### Randomization/blinding

After enrolment, participants will be randomly assigned to LUS-monitored or standard care group by the use of block-generator software. Both the clinicians who will perform and score LUS, and the patients’ family will be blinded to randomization.

The child neurologist and the SLP will be informed of the result of LUS only in the LUS-m group and will include that result to impact on feeding care (postural- hygiene care adaptation, thickening fluids or drugs available for GERD). LUS results in the SC-m group will be available only at the time of data analyses.

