### LUS procedure/Equipment

The intervention is a LUS-monitored (before and after) feeding trial (the “after” evaluation will be within 15 min the end of the feeding procedure). A further LUS evaluation will be performed at a distance of 3 h, before the next meal to check for resolution of eventual after-meal abnormalities. All meals will be monitored by pulse-oximetry and video recorded.

Lung ultrasound exam will be performed based on a previously described scanning scheme in children [25], as indicated in Fig. 2. Commercially available portable machines with a linear probe (9–12 MHz) with specific setting for infants will be used (Lumify, Philips Medical Systems, Andover, MA, USA). Acquired images and movies will be saved in both groups but only available for final analyses in the SC-m group. In detail, the thorax will be divided into 3 major scanning areas (anterior, lateral, and posterior) divided by the parasternal, anterior axillary, and posterior axillary anatomical lines on both the right end the left hemithorax. A deaeration score will be used to classify each LUS exams, taking into account the following signs in each scanning area: the number of B-lines; the appearance of the pleural line; presence of C-lines; presence of small peripheral sub-pleural consolidations; presence of large consolidations; presence of pleural effusion. A deareation score will be calculated before and after the meal, so when the after-meal score will be different from pre-meal score (more than 10%), an intervention will be assigned to modify feeding performance and reported as medical, postural or food consistencies adaptation in the experimental group.

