### Assessments

Infants will be assessed for outcomes according to the timeline. At T0, neurological information will be collected by using the Hammersmith Infant Neurological Examination (HINE) [26]; Alberta Infant Motor Scale (AIMS, [27]), GMFCS E&R [28]. The clinical measures used are standardized and validated for use across a wide age range.

Clinical primary outcomes will be rate of pulmonary illness (including pneumonia, wheezing, chronic cough, and apnea rate) and performance at growth curves (according to WHO growth standards, eventually age-corrected because of premature birth, or according to specific syndrome growth standards as recommended by ESPGHAN [9]. Between T0 and T2, parents will be asked to fill a detailed respiratory infection-diary for respiratory illness rate calculation (information collected at both T1 and T2). We will consider the exact, separate number of upper and lower airways infection and detect patients suffering from RRI (Recurrent Respiratory Infections), according to the most recent definition, i.e. i) 6 or more airways infection/year (at least 1 pneumonia, even severe), or ii) 2 pneumoniae even not severe but radiologically confirmed [29].

Primary outcome measure will include LUS score at T1. We assume that a better baseline detection of aspiration will result in better management with a reduction of pulmonary abnormalities detected by LUS at primary endpoint. Secondary outcomes collected at T1 will include chronic pain assessment (parents-report measures, behavioral measures including the Non-communicating Children’s Pain Checklist, and physiological measures) [30] and parents’ stress by a parent stress questionnaire (Parenting Stress Index PSI) [31]. At T0 and T2 laboratory exams will be performed to evaluate general and nutritional status (blood cells count, reticulocytes count, ferritin, total serum protein electrophoresis, prealbumin, transferrin, TSH, FT3, FT4, sodium, potassium, calcium, phosphorus, folates, vitamin B12, 25-OH-vitamin D, C-reactive protein, erythrocyte sedimentation rate, Insulin-like Growth Factor I) and quantitative ultrasound (QUS) also, in order to quantify bone mineralization.

VFSS and FEES data will be collected when performed according to multidisciplinary clinical indications, compared in frequency of execution between groups, and their results will be compared to LUS findings.

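### The caregiver blind is vulnerable: scan-driven feeding changes occur only in the LUS-monitored arm, and parents supply the illness diary, part of the pain assessment and the stress score

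*Protocol article*

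**What the plan says.** The Background and Study design sections both describe the trial as double-blinded. Table 1 specifies "Double blind (caregiver, outcomes assessor", and Randomization/blinding states: "Both the clinicians who will perform and score LUS, and the patients’ family will be blinded to randomization".

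The treating team is handled differently by arm: "The child neurologist and the SLP will be informed of the result of LUS only in the LUS-m group", and they "will include that result to impact on feeding care (postural- hygiene care adaptation, thickening fluids or drugs available for GERD". Standard-care (SC-m) results are held back until the data are analysed. LUS procedure/Equipment gives the trigger: "when the after-meal score will be different from pre-meal score (more than 10%), an intervention will be assigned to modify feeding performance". The resulting change is to be "reported as medical, postural or food consistencies adaptation in the experimental group".

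Under Assessments, the rate of pulmonary illness is a clinical primary outcome, and "parents will be asked to fill a detailed respiratory infection-diary for respiratory illness rate calculation" between T0 and T2. Secondary outcomes at T1 include a pain assessment with a parent-report component and the Parenting Stress Index (PSI), a parent questionnaire.

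**The concern.** Withholding the allocation from a family is not the same as concealing it. Here the arms differ in what the treating clinicians do after a scan, and what they do is visible to whoever feeds the child. A parent who has been told about the study procedures and then receives new feeding instructions after a monitored meal has a cue to the arm.

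That parent is also the source of some outcome data. For the diary and the PSI the caregiver is in effect the assessor, so if the caregiver blind weakens, the assessor blind weakens with it. A belief about the arm could alter what is noticed, written down or felt. A reader who relies on the double-blind label would give these outcomes the same protection as the LUS score, which they do not have.

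**Working it through.** No figure in the article bears on this point, so there is nothing to reproduce. The check sets the statements side by side.

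**1. What is the same in both arms.** Both groups have the same follow-up with monitored meals: baseline, three in the first 3 months, and one at T2, so 1 + 3 + 1 = 5 scheduled occasions (Study design). Being scanned does not reveal the arm. Nothing says that families see the score.

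**2. What differs.** Only in LUS-m does the result reach the neurologist and SLP. Only in LUS-m does a change of more than 10% between the pre-meal and after-meal scores mean that "an intervention will be assigned to modify feeding performance".

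**3. Whether a family would notice.** The article does not say who carries out the change. The listed adaptations concern positioning, thickened fluids and reflux drugs in children aged 0 to 6 years, who are seen about monthly. That the family sees or applies them between visits is an inference, but a strong one. Procedure adds that parents receive detailed information on the study before consent.

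**4. How reliable the cue is.**
- In LUS-m, a child whose score changes by 10% or less triggers no assigned intervention, so that family gets no scan-driven cue at that visit.
- In SC-m, feeding advice can still follow a visit, because standard care includes clinical feeding evaluation and empirical trials, and study visits are merged with clinical follow-up where possible.
- New advice after a scan is therefore informative about the arm but does not identify it.

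**5. Which outcomes pass through the parent.**

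| Outcome (Assessments) | Status | Exposed by this route? |
|---|---|---|
| LUS score at T1 | Primary; basis of the sample size | No; operators and scorers blinded |
| Growth | Primary | No; judged against growth standards |
| Pulmonary illness rate | Primary | Yes; based on the parent diary, though it includes pneumonia as well as wheeze and cough |
| Pain | Secondary | Parent-report part only; there are also behavioural and physiological measures |
| PSI | Secondary | Yes |

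**6. Size, by assumption only.** Let u be the proportional change in diary reporting among LUS-m families who act on the cue, and q the share of LUS-m families who do so. With equal true rates and no reporting change in SC-m, the observed rate ratio is 1 + q × u. The documents give neither value.
- Assume a true rate of 2.0 events per child over 3 months in both arms, q = 1, and under-reporting of 10% to 20%. LUS-m then shows 2.0 × 0.9 = 1.8 to 2.0 × 0.8 = 1.6, a ratio of 1.8/2.0 = 0.90 to 1.6/2.0 = 0.80.
- Assume instead that advice makes parents more watchful and reporting rises by the same 10% to 20%. The ratio is 2.2/2.0 = 1.10 to 2.4/2.0 = 1.20.
- With q = 0 the ratio is 1.00.

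The result only returns the assumption put in. It shows that a distortion can arise without a true effect, not that one will.

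**The case against.** The strongest reply is that scanning every SC-m child with the result withheld works much like a sham procedure, and that advice can be given in either arm. This stands, and it rules out saying that the blind is broken. A reader might infer that families will know their arm; the documents do not support that, because the cue misleads in both directions.

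A second reply is that the label is not bare: Table 1 names who is blinded, and Randomization/blinding openly says that the neurologist and SLP receive LUS-m results. This also stands in part, since the unblinded treating team is disclosed. What is not acknowledged is that the team's arm-specific actions bear on the family's blind.

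A third reply is that this is a journal article, and that advice scripts or a check on blinding may be in the full protocol. That is fair, and their absence here is not counted as a fault. The point rests on what the article does state: an unqualified caregiver blind, beside a mechanism that puts it at risk.

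A reader might also infer that any bias must favour LUS-m, through parents reporting fewer symptoms once they believe the child is being managed. Nothing in the documents establishes this. More advice could equally raise vigilance, diary entries or stress.

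**Conclusion.** The point holds in a limited form. The caregiver blind is vulnerable for one primary outcome (the diary-based illness rate), the parent-report part of one secondary outcome (pain) and another secondary outcome (the PSI). It rests on one inference, that families see or apply the feeding changes, and on no assumption about the direction of bias, which is unknown, as is its size.

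It would go too far to treat every LUS-m family as exposed, since those with no triggered change get no scan-driven cue. It would also go too far to extend the concern to the whole trial: the LUS score, growth and the pain measures that do not come from parents are not affected this way. The double-blind description claims more for the parent-reported outcomes than the design can secure, and should be corrected.

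**What to change.** - **Same-format advice in both arms.** At every study visit, give each family a written feeding-advice record in one common format, including a no-change entry, with no mention of LUS. This standardises the form only; the content and timing of clinical care stay as they are.
- **Sensitivity analysis.** Keep the primary illness count as defined, since recruitment is under way. Record for each diary event whether there was a medical contact or record, and prespecify a sensitivity analysis of the illness rate limited to those events. State its limit: contacts may themselves be influenced by the unblinded treating team.
- **Accurate wording.** In Background, Study design and Table 1, replace the double-blind label with a statement that LUS operators and scorers are blinded, families are not told their allocation, and the treating neurologist and SLP are not blinded. Interpret the parent-reported outcomes accordingly.
- **Optional.** Ask families at T1 and T2 which arm they think they are in, and report the answers by arm.

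The cost is one extra form, one diary field with the effort of completing it, and one sensitivity analysis that will be less precise because it counts fewer events.
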